#### Sample size determination

Based on a small effect size of 0.20 (Cohen’s f) for an improvement in relative VO_2_peak after HIIT versus no HIIT [42], performing a priori sample size calculation for a repeated measures analysis of variance with an expected correlation of 0.50 between measurements, alpha of 0.05 and 85% power of detection, a total sample size of 60 women will be required (G*Power, version 3.1.9.2). The sample size will be doubled to account for further planned analysis of secondary outcomes in sub-groups of normal and high BMI women (HIIT normal BMI, HIIT high BMI, CON normal BMI, CON high BMI). The target sample size will be therefore be 120 women exclusive of drop outs.

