#### Randomisation

All eligible women will be classified as being in either one of two BMI groups (normal BMI: 20-24.9 kg/m^2^, *n* = 60; high BMI: 25-35 kg/m^2^, *n* = 60). Women will then be randomized into either a control group (CON) or a group that will follow the HIIT protocol (HIIT) resulting in four groups of women: high BMI control (CON-H; *n* = 30), normal BMI control (CON-N; n = 30), high BMI HIIT (HIIT-H; n = 30) and normal BMI HIIT (HIIT-N; n = 30). The randomisation procedure for the intervention groups will be done using Microsoft Excel RANDBETWEEN function. The RANDBETWEEN function (=RANDBETWEEN (1,2)) is able to assign participants into one of the two groups, in this instance 1 = CON and 2 = HIIT. Two random sequences of 120 numbers each (group 1 or 2) is generated for each BMI category (high and normal). The sequences were generated by an investigator who is not involved in the data collection procedures. Upon enrolment of a participant into the study, the group allocation of the participant is revealed to a non-blinded research assistant responsible for data collection.

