### Statistical analysis

Data will be analysed using Stata (version 15.1, StataCorp LLC, TX, USA). Data will be expressed as mean (SD) or as median (IQR). Data will be tested for normality (Shapiro-Wilks test) and relevant parametric or non-parametric tests will be applied to the testing of hypotheses. Patient characteristics will be reported for all those recruited into the study as well as those remaining in the study at the end of the intervention using descriptive statistics (mean and standard deviation or median and interquartile range or percentages). A linear mixed model analysis will be used to determine the effects of the HIIT intervention on body composition measures and cardiometabolic parameters with fixed factors of exercise group and time and a random factor of participant. The variance-covariance structures will be selected based on Bayes Information Criterion and the unstructured variance-covariance used. In the case of data that is not normally distributed a generalised linear mixed model will be used. Secondary outcome data between the four groups of women will be analysed in a similar way. Participant age and baseline physical activity level will be included in the models as covariates. Statistical significance will be set at 0.05 and effect sizes will also be reported.

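### The HIIT versus control model uses baseline as an unconstrained response and omits the BMI stratum; conditioning on both is a free improvement

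*Protocol article*

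**What the plan says.** All places are in the protocol article.

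- **Statistical analysis, model.** A linear mixed model is fitted "with fixed factors of exercise group and time and a random factor of participant". The sentence states its purpose as to "determine the effects of the HIIT intervention on body composition measures and cardiometabolic parameters"; VO2peak is not named there.
- **Statistical analysis, covariates.** "Participant age and baseline physical activity level will be included in the models as covariates". No other covariate is named.
- **Statistical analysis, four groups.** "Secondary outcome data between the four groups of women will be analysed in a similar way". Sample size determination defines these groups as "sub-groups of normal and high BMI women (HIIT normal BMI, HIIT high BMI, CON normal BMI, CON high BMI").
- **Randomisation.** "All eligible women will be classified as being in either one of two BMI groups", with 60 women planned in each, and allocation is made within each group. "The randomisation procedure for the intervention groups will be done using Microsoft Excel RANDBETWEEN function", which draws 1 or 2 independently for each woman; no blocking is described.
- **Outcome measures and Table 1.** Every outcome is measured before and after the intervention. Body mass and waist:hip are also measured every 4 weeks.
- **Sample size determination.** The calculation is for a "repeated measures analysis of variance with an expected correlation of 0.50 between measurements", with Cohen's f of 0.20, alpha 0.05 and 85% power. It gives 60 women, doubled to 120 for the BMI subgroups.

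**The concern.** Two variables that a statistician would expect in the treatment model are missing from the covariate list: the outcome's own baseline value and the factor used to stratify randomisation.

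Baseline is one of the levels of time, so the model treats it as a response and lets the arms have different baseline means. With two time points, the group-by-time contrast then reduces to a difference in mean change. When the pre-post correlation is well below 1, a change score carries the noise of both measurements, and conditioning on baseline removes part of it.

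The two-arm comparison pools both BMI strata without a stratum term. The primary outcome is oxygen uptake per kilogram of body mass, so BMI is plainly relevant to it. Because the draws are unblocked, stratification does not force the arms to have the same BMI mix.

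At stake are the width of the intervals and protection against chance imbalance. The validity of the analysis is not in question.

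**Working it through.** **Inputs from Sample size determination.** f = 0.20, ρ = 0.50, alpha = 0.05, power 85%, N = 60 required and 120 targeted. In a layout of two groups by two times, f = D/4, so the difference in change is D = 4 × 0.20 = 0.80 SD.

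**Step 1: reproduce the plan's figure.** For the group-by-time interaction, the noncentrality is λ = N·m·f²/(1−ρ) = N × 2 × 0.04/0.50 = 0.16N, with 1 and N−2 degrees of freedom.

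- N = 58: power 0.849
- N = 60: power 0.861

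The smallest N in equal groups is 60, as stated. So the sample size rests on the change-score contrast, and the steps below read the mixed model as testing group by time.

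**Step 2: compare variances.** In units of SD², the change score has variance 2(1−ρ) = 2 × 0.50 = 1.00. Conditional on baseline, the variance is 1−ρ² = 1 − 0.25 = 0.75. The ratio is (1+ρ)/2. Interval width scales with √0.75 = 0.866, so intervals are about 13% narrower.

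The documents give only ρ = 0.50; the other values are assumed, to show the range:

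| ρ | Variance ratio | Reduction |
|---|---|---|
| 0.3 | 0.65 | 35% |
| 0.5 | 0.75 | 25% |
| 0.7 | 0.85 | 15% |
| 0.8 | 0.90 | 10% |
| 0.9 | 0.95 | 5% |

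The ratio is a large-sample figure. In 20,000 simulated trials with N = 60 and ρ = 0.50, the variance in units of 4·SD²/N was 1.00 for the group-by-time contrast and 0.777 for ANCOVA, a reduction of about 22%.

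**Step 3: power at ρ = 0.50.** With residual variance v, λ = N·D²/(4v); the baseline-adjusted test has N−3 degrees of freedom.

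| D | N | Change score | Baseline-adjusted |
|---|---|---|---|
| 0.8 SD (protocol) | 60 | 0.861 | 0.940 |
| 0.8 SD (protocol) | 120 | 0.991 | 0.999 |
| 0.4 SD (assumed; not in the documents) | 120 | 0.584 | 0.709 |

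At 0.8 SD, the N for 85% power falls from 60 to 46. Sixty is also the planned size of each BMI stratum, so the first row describes a comparison within one stratum.

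**Step 4: what the BMI stratum adds.** The same simulation assumed that the strata differ by 0.5 SD in level, equally before and after the intervention.

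- Change score, with stratum by time added: variance 1.02 against 1.00, so no gain.
- ANCOVA, with stratum added: 0.776 against 0.777, so almost no gain.
- In one fitted mixed model, a BMI main effect left the group-by-time estimate (0.682) and its standard error (0.242) unchanged.

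If stratum explained a further 2%, 5% or 10% of the variance left after baseline (assumed), power at N = 60 and 0.8 SD would go from 0.940 to 0.944, 0.950 or 0.960.

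**Step 5: how much BMI imbalance the draws allow.** With 60 women per stratum and independent 1:1 draws, the number allocated to HIIT in a stratum has variance 60 × 0.25 = 15. The difference between strata in that number has SD √30 = 5.48. The arms' shares of high-BMI women therefore differ with an SD of about 5.48/60 = 0.09, or 9 percentage points. An exact binomial calculation gives a difference of 10 points or more in about 32% of trials.

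**The case against.** The strongest reply is that nothing here is wrong. Baseline is in the model as a response, group by time with a random participant effect is a standard and unbiased analysis, and on the protocol's own effect and target the primary comparison has power of about 0.99 either way. The article condenses a fuller plan, and its covariate sentence does not say that the list is complete. All of this stands, and it makes the point one of efficiency. The article does, however, name the covariates, so the choice as stated can be improved.

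Four stronger readings are tempting, and the documents do not support them:

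- **That baseline data are thrown away.** They are used, but less efficiently than they could be.
- **That omitting BMI makes intervals much wider.** A constant BMI effect on level cancels from the group-by-time contrast, so imbalance matters there only if BMI also predicts change. The share of VO2peak variance due to BMI, and its rank as a predictor, are not documented.
- **That BMI stratum is ignored throughout.** It is part of the group factor in the four-group analysis of secondary outcomes; it is absent only from the two-arm model.
- **That the primary comparison is underpowered without adjustment.** This follows only for effects smaller than the protocol's, such as the assumed 0.4 SD.

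Two limits of scope also stand. The figures apply directly to outcomes measured twice, not to body mass and waist:hip. And because the model sentence does not name VO2peak, applying it to the primary outcome is a reading, though the sample size calculation supports it.

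**Conclusion.** The point holds as a free improvement to a valid analysis. As written, the two-arm model neither conditions on the outcome's baseline nor constrains the arms to a common baseline mean. At ρ = 0.50 that forgoes about a quarter of the variance in large samples, and less if the true correlation is higher. The gain is useful where 60 women carry a comparison and small for the primary comparison at 120. The case for BMI stratum is fidelity to the randomisation and protection against the imbalance that unblocked draws allow; the precision gain is slight.

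The conclusion assumes that the tested contrast is group by time. The article lists group and time without an interaction. That is probably condensation, and it is a separate matter from the covariates.

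**What to change.** In every HIIT versus control model, and explicitly in the model for VO2peak:

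1. Condition on the outcome's baseline value, either by ANCOVA of the post-intervention value or by a mixed model with equal baseline means across arms.
2. Include BMI stratum. If baseline stays a response, add stratum by time, because a main effect alone cannot alter the group-by-time contrast.
3. Keep age and baseline physical activity. If baseline stays a response, the same remark on time interactions applies to them.

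For body mass and waist:hip, the constrained mixed model accommodates the four-weekly visits. The cost is a few model terms and a sentence in the analysis plan, with no extra data or participants. It should be fixed before outcomes are analysed by arm, so that the adjustment cannot be chosen on the results.

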### Outcome measures

The primary outcome of the trial is a change in cardiorespiratory fitness after the 14-week HIIT intervention. Secondary outcomes are changes in body composition, cardiovascular health and metabolic biomarkers of health, as well as measures of feasibility and physical activity and sedentary behaviour levels. Both primary and secondary outcomes will be measured before and after the 14-week intervention (Fig. 2).

Table 1 summarises the outcome measures to be made and the time points at which they will be measured during the study.

**Table 1 Tab1:** Indication of physiological variables measured and timepoints of each measurement

Variable	Timepoints measured
*Primary outcome*	
Peak VO_2_, HR at peak VO_2_, HR at 65 and 85% peak VO_2_	Baseline, post-intervention
*Secondary outcomes*	
Anthropometry	
Skinfolds	Baseline, post-intervention
Body mass and waist:hip	Baseline, every 4 weeks during intervention, post-intervention
Brachial blood pressure	Baseline, post-intervention
Central blood pressure and arterial stiffness	Baseline, post-intervention
Echocardiography	Baseline, post-intervention
Biomarkers of metabolic and cardiovascular health	Baseline, post-intervention
Feasibility (adherence and dropout rate)	Baseline, every 4 weeks during intervention, post-intervention
Accelerometry	Baseline, every 4 weeks during intervention, post-intervention

*VO*_*2*_*peak* Peak oxygen consumption, *HR* Heart rate

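### Age and baseline activity, read as main-effect covariates, cancel from the HIIT effect on change, so the stated adjustment does almost nothing for that effect

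*Protocol article*

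**What the plan says.** The Statistical analysis section of the protocol article specifies a linear mixed model for the body composition and cardiometabolic outcomes. Its terms are described as a model "with fixed factors of exercise group and time and a random factor of participant". Its covariate sentence reads "Participant age and baseline physical activity level will be included in the models as covariates". The four BMI-by-arm groups are to be analysed in a similar way. An unstructured covariance is named, and there is a fallback: "In the case of data that is not normally distributed a generalised linear mixed model will be used".

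The responses are repeated measures. Under Outcome measures, "Both primary and secondary outcomes will be measured before and after the 14-week intervention"; Table 1 adds four-weekly values for body mass and waist:hip. The same section defines the primary outcome as a change, and the Discussion compares changes with those of the controls.

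The text writes neither a group-by-time term nor a covariate-by-time term.

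**The concern.** The question the trial asks of this model is whether women in the HIIT arm change more than controls. That is a difference between arms in a within-woman difference. Age and baseline activity are fixed for each woman, so a main effect shifts her baseline and week-14 values equally and vanishes when one is subtracted from the other.

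If the analyst follows the sentence in its usual sense, the model carries two covariates that adjust the level of the outcome and leave the HIIT effect on change alone. Any precision these variables could give is forgone, and a chance difference between arms in age or activity is not corrected in the effect. A reader who sees age and activity listed as covariates may also think the effect has been adjusted for them.

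**Working it through.** **Inputs from the protocol.** Model terms and covariates: Statistical analysis. Visits: Outcome measures and Table 1. Effect size f ("small effect size of 0.20"), correlation ("expected correlation of 0.50 between measurements"), "alpha of 0.05 and 85% power of detection", 60 women before doubling and a target of 120: Sample size determination. Four groups of 30: Randomisation.

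**Inputs assumed.** The share R² of the variance of change explained by the two covariates (0%, 5%, 10%, 20%) and the dropout rate (0%, 20%, 40%). The protocol gives neither.

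**1. Which contrast the trial was sized for.** For a within-between interaction with 2 groups and m = 2 times, lambda = f² × N × m / (1 − rho) = 0.04 × 60 × 2 / 0.5 = 9.6, with 1 and 58 degrees of freedom. Power is 0.861 at N = 60 and 0.849 at N = 58, so the stated 60 is reproduced. A test of the time-averaged group difference would need 172. The pure time effect also gives 60, but the stated comparison is HIIT against no HIIT, so the interaction, that is, the difference in change, is the natural target.

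**2. The algebra.** With t = 0 at baseline and t = 1 at week 14:

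Y(i,t) = a + bG·G(i) + bT·t + bGT·G(i)·t + c1·age(i) + c2·activity(i) + u(i) + e(i,t)

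Subtracting the two visits:

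Y(i,1) − Y(i,0) = bT + bGT·G(i) + e(i,1) − e(i,0)

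The terms in c1 and c2 are gone. With complete data the estimate of bGT is the difference in mean change, with or without the covariates. The same subtraction applies in the four-group model.

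**3. Numerical check of the cancellation.** Simulated data, 120 women, two visits, REML with a random intercept, 30 data sets (assumed effect on change 2, residual SD 3, covariates predicting level but not change). The largest difference between adjusted and unadjusted bGT was 7e-14; the SE was 0.776 in both. In one further data set, with covariates explaining 20% of the variance of change, bGT was 0.339 (SE 0.190) both ways. With an unstructured covariance it was 0.339 (SE 0.189) both ways.

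**4. Where the cancellation is not exact** (settings of the 30-data-set check):

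| Situation | Mean shift in estimate | Largest shift | SE without → with main effects |
|---|---|---|---|
| bGT, 20% dropout | 0.12 | 0.32 | 0.860 → 0.855 |
| bGT, 40% dropout | 0.12 | 0.44 | 0.967 → 0.957 |
| bGT, common baseline mean, complete data | 0.12 | 0.36 | 0.714 → 0.692 |
| Group coefficient, group + time only, complete data | 0.31 | 0.91 | 0.902 → 0.759 |

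With dropout, the mean shift is about 0.14 of the SE at 20% (0.12 / 0.860) and 0.12 of it at 40% (0.12 / 0.967). The last row concerns a different quantity: without an interaction, the group coefficient targets the average over both visits, here (0 + 2) / 2 = 1, and not the effect on change of 2.

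**5. What entering the covariates with time could gain.** The SE of the change contrast is multiplied by about sqrt(1 − R²), which is worth 120 / (1 − R²) women analysed without adjustment.

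| Assumed R² | sqrt(1 − R²) | SE reduction | Equivalent N |
|---|---|---|---|
| 0% | 1.000 | none | 120 |
| 5% | 0.975 | 2.5% | 126 |
| 10% | 0.949 | 5.1% | 133 |
| 20% | 0.894 | 10.6% | 150 |

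Simulation agrees: SE 0.187 → 0.183 at 5% and 0.204 → 0.184 at 20%. At 0% it rose slightly, 0.180 → 0.182 in one set of runs and 0.776 → 0.779 in the check of step 3.

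**The case against.** The strongest reply is that the protocol nowhere says the covariates enter as main effects only. A journal article may leave interaction terms to an analysis plan, and it would be selective to supply the unwritten group-by-time term while withholding covariate-by-time terms. This stands in part: the main-effect form is an inference. It is the usual meaning of the phrase, however. Group-by-time is implied by an aim framed as change against controls and by the sample size calculation, whereas nothing implies covariate-by-time. The article chose to state both the model and the adjustment, and as stated the one does not deliver the other.

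Three limits stand in full.

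- A reader might infer that the covariates can never alter the HIIT estimate. That is too strong. Exact equality needs a linear model, a group-by-time term, freely estimated baseline means and complete data. The protocol expects dropout and allows a generalised model, where exact cancellation is not assured under a non-identity link.
- The gain is conditional. No figure in the protocol supports 5% to 20%, and if the covariates predict only the level of an outcome, the fix gains nothing in precision.
- Chance imbalance is ordinary sampling error, already counted in the SE. Adjustment would remove part of it; its absence adds no further error.

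**Conclusion.** The point holds as a weakness of specification. Read as main effects, age and baseline activity leave the HIIT effect on change and its SE untouched with complete data, and alter them little with dropout. The cost is forgone precision: nil if the covariates explain none of the change, and an SE about 2.5% to 11% higher than it need be if they explain an assumed 5% to 20%.

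Two further inferences should be resisted. The HIIT effect is not biased by this: randomisation protects the unadjusted change contrast. Nor does the text establish that the primary VO2peak analysis is affected, because the mixed model is named for body composition and cardiometabolic parameters. If the same model is meant for VO2peak, the point carries over.

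The cancellation rests on algebra. The dropout and precision figures rest on the assumptions stated.

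**What to change.** Amend the covariate sentence in Statistical analysis to do two things:

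- name group-by-time as the treatment contrast;
- enter age and baseline activity together with their interactions with time.

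With complete pre/post data, a regression of the change on group, age and activity is equivalent. ANCOVA of the week-14 value on group, age, activity and the baseline value of the same outcome is also sound. A week-14 regression that omits the baseline outcome is not a substitute: in simulation its estimate differed from the change-based one by about 0.15 SD on average. Make the same change in the four-group models.

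The cost is one sentence and two extra model terms per outcome, with no new data. If the covariates turn out not to predict change, the SE rises negligibly, by about 1% in the runs above (0.180 → 0.182).

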## Methods/design

### Study objectives

This randomised controlled trial will compare the effects of a 14-week low-volume high-intensity interval training intervention on cardiorespiratory fitness, body composition and cardiometabolic health in women of normal body mass and women with overweight/obesity. In addition, adherence to and drop-out rate of the intervention will be measured to determine feasibility. We hypothesise that at the end of the 14-week intervention, women with overweight/obesity performing HIIT will have significant changes in their cardiorespiratory fitness and cardiometabolic health regardless of a change in body composition. We also expect that a low-volume HIIT intervention will be feasible in this cohort of women.

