#### Cardiovascular health measures

##### Brachial blood pressure

Resting brachial blood pressure (BP) will be measured prior to any testing or exercise after a five-minute rest period. The average of two measurements will be taken with an automated BP monitor (SpaceLabs, Redmond, WA). If the first two measures for either the systolic or diastolic blood pressures differ by more than 5 mmHg, a third measurement will be taken to determine the mean blood pressure.

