## Discussion

This study intends to determine whether 66 min per week of own-body weight HIIT (which is 9 minutes/week less than the current WHO recommended guidelines of 75 min of vigorous activity per week) performed at home has the ability to 1) improve cardiorespiratory fitness, 2) result in cardiometabolic benefits regardless of BMI and 3) be a feasible method of engaging in exercise. The study also aims to determine whether the body composition and cardiometabolic changes in women with overweight/obesity and normal body mass are different compared to the non-exercising controls. There is evidence that short duration high intensity exercise has benefits to certain aspects of cardiovascular health [60, 61] however these studies were conducted in healthy males [60] and in patients with metabolic syndrome [61] respectively. Supervised HIIT has been shown to be as beneficial if not more beneficial compared to MICT on various parameters of health including blood lipid profiles, fasting glucose and insulin levels and blood pressure [37, 40, 41]. The time dedicated to supervised HIIT interventions however is often over and above the minimum recommended dose prescribed for the maintenance of cardiometabolic health [40]. As one of the reasons cited for people not participating in regular exercise being a lack of available time [28], investigation into the efficacy of low volume but high intensity exercise on cardiometabolic health is needed to determine whether it is possible for people to minimise their required engagement in exercise for health including the need for generally healthy people to be supervised. HIIT may be especially beneficial for women, a group that experiences inequity in physical activity engagement [62]. More long-term controlled trials investigating other markers of cardiometabolic health risk are needed in women to begin to explore the mechanisms for the efficacy of HIIT. Furthermore, most studies have used treadmill or cycling protocols and if a paradigm shift in the general population is to occur towards increasing levels of physical activity in habitual life, then more studies are needed on the efficacy of alternative exercise protocols on health in various populations in realistic settings. Only one study has investigated the effect of a one-year home-based HIIT on health in overweight adults. However the study participants showed poor compliance to the intervention and healthy controls were not included in the study [48].

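### The cardiometabolic hypothesis rests on at least 37 unranked secondary variables under one 0.05 level, so an isolated significant result could be read as support for it

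*Protocol article*

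**What the plan says.** The Study objectives section hypothesises that, at the end of the intervention, "women with overweight/obesity performing HIIT will have significant changes in their cardiorespiratory fitness and cardiometabolic health regardless of a change in body composition". The Discussion lists, as the second of three questions the study intends to settle, whether the programme can "result in cardiometabolic benefits regardless of BMI".

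The Outcome measures section separates primary from secondary: "The primary outcome of the trial is a change in cardiorespiratory fitness after the 14-week HIIT intervention", and "Secondary outcomes are changes in body composition, cardiovascular health and metabolic biomarkers of health, as well as measures of feasibility". No secondary variable is ranked above another.

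The Statistical analysis section applies a linear mixed model to the body composition and cardiometabolic measures and then states a single criterion: "Statistical significance will be set at 0.05 and effect sizes will also be reported". It adds that "Secondary outcome data between the four groups of women will be analysed in a similar way".

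**The concern.** Cardiometabolic health is not one endpoint. It covers brachial pressure, central pressure and arterial stiffness, echocardiography, and blood markers, each with several variables. The hypothesis predicts significance for this whole area without saying which variable, how many variables or which direction would count. With one 0.05 level for all of them, nothing stated prevents a single p<0.05 among many tests from being presented as support for the cardiometabolic part of the hypothesis.

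At stake is one of the three questions the trial sets itself. The primary comparison on fitness is not affected.

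**Working it through.** **The plan's own figure.** The only size calculation is for relative VO2peak (Sample size determination): f = 0.20, correlation 0.50, two measurements, alpha 0.05, power 85%, N = 60. For a two-group by two-time interaction, the noncentrality is f² × N × m / (1 − ρ) = 0.04 × 60 × 2 / 0.5 = 9.6 on 1 and 58 degrees of freedom. This gives power 0.861, and 60 is the smallest even N that reaches 0.85. The figure reproduces. It covers one test at 0.05. The article gives no error rate for the secondary family.

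**Counting the variables.** The count is minimal, from the measurement sections.

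| Section | Variables | Count |
|---|---|---|
| Brachial blood pressure | systolic and diastolic, as in "If the first two measures for either the systolic or diastolic blood pressures differ by more than 5 mmHg" | 2 |
| Central blood pressure and arterial stiffness | PWV, reflected wave index, central pressure (counted once), forward wave, reflected wave, aortic pulse pressure, PPamp | 7 |
| Echocardiography | septum, posterior wall and LV internal dimension, each in diastole and systole (6); E/A, E/e', e'/a' (3); circumferential and longitudinal strain and strain rate (4) | 13 |
| Cardiometabolic biomarkers | 4 lipids; glucose, insulin, IL-6, hs-CRP, adiponectin, leptin, chemerin (7); ICAM-1, VCAM-1, E-selectin (3); HOMA-IR (1) | 15 |
| Total | | 37 |

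The component Doppler velocities, body composition, accelerometry and the four-group analyses are left out.

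**False-positive rate if HIIT affects none of the 37.** Sidedness is not stated, so two-sided tests are assumed. The article gives no correlations between outcomes, so a range is assumed.

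- Independent tests, either direction: 1 − 0.95^37 = 0.850.
- Independent tests, favourable direction only (0.025 each): 1 − 0.975^37 = 0.608.
- Expected number of chance results at any correlation: 37 × 0.05 = 1.85 in either direction and 37 × 0.025 = 0.925 in the favourable direction.
- Common correlation ρ, either direction: 1 − ∫ φ(u) [Φ((1.96 − √ρ·u)/√(1−ρ)) − Φ((−1.96 − √ρ·u)/√(1−ρ))]^37 du. For the favourable direction, drop the second Φ term. Each variable is oriented so that positive means benefit.

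| Assumed correlation | Either direction | Favourable direction |
|---|---|---|
| 0 | 85% | 61% |
| 0.3 | 72% | 39% |
| 0.5 | 55% | 28% |
| 0.8 | 27% | 14% |

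A simulation with correlation 0.5 within the four measurement domains and 0.1 between them gives about 70% in either direction and 40% in the favourable direction. With ten smaller blocks (0.3 to 0.8 within, 0 to 0.2 between), the ranges are 64% to 83% and 35% to 57%.

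**Against the nominal rate.** The lowest either-direction figure is 0.27 / 0.05, about 5 times nominal. The lowest favourable-direction figure is 0.14 / 0.025, also between 5 and 6 times.

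**The case against.** Several objections carry weight.

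- **Benefit versus any difference.** A reader might infer from the 85% or 55% that a false claim of benefit is more likely than not. Those figures count significance in either direction. In the favourable direction the rate passes one half only when the tests are independent or nearly so. Independence is not credible, since HOMA-IR is computed from glucose and insulin, and PPamp from pulse pressures. For some variables, such as wall thickness, no direction of benefit is defined. This objection stands.
- **The success rule.** A reader might infer that the plan treats any one significant variable as confirmation. It nowhere says so. The hypothesis also joins fitness and cardiometabolic health, so a null VO2peak result would defeat it as a whole. This stands. The defect is that no rule is given, not that a bad one is written down.
- **Hierarchy.** A reader might infer that there is none. In fact the Background ranks fitness first, the sample size is built on VO2peak alone, and Table 1 labels the cardiometabolic measures secondary. The gap lies only within the secondary family.
- **Four-group analyses.** It is tempting to multiply the tests by BMI stratum. The article says only that the four groups will be analysed similarly and specifies no within-stratum tests, so no larger figure is supportable.
- **Unseen analysis plan.** A condensed article may leave multiplicity rules to another document, and the lack of an adjustment method alone would be no finding. But the article itself states both a hypothesis of significance over an undefined set and a single level for it. A later adjustment rule would leave the published hypothesis as it is. This objection does not remove the point.

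**Conclusion.** The point holds in a limited form. A prediction of significance covers at least 37 variables, none of them designated as decisive, with one 0.05 level for all. If HIIT affects none of them, at least one significant result in either direction has probability 27% to 85% over assumed common correlations from 0.8 down to 0, and it exceeds one half up to a correlation of about 0.5. The corresponding favourable-direction range is 14% to 61%. The documents do not show that a false claim of benefit is more likely than not.

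These figures rest on the minimal count of 37, two-sided tests, no true effect on any variable, and correlations that the article does not supply. The primary analysis is untouched, but the cardiometabolic claim should be put right before results are reported.

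**What to change.** In the Statistical analysis section, state that HIIT versus CON on relative VO2peak is the only confirmatory test at 0.05. State that all secondary outcomes and all four-group BMI analyses are exploratory and will be reported as estimates with 95% confidence intervals. Reword the cardiometabolic part of the hypothesis in Study objectives, and the second question in the Discussion, so that they speak of estimating the effect and not of significant changes or established benefit.

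If a confirmatory cardiometabolic claim is wanted, an optional alternative is to name a few key variables and test them with multiplicity control after the primary. Holm's procedure on one variable per domain is one acceptable design among several. Because data collection is under way and the data collector is unblinded, the choice should be dated and recorded before the analyst's group labels are restored.

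The cost is wording only, with no new data or participants. The downside is that an isolated secondary p<0.05 can no longer be reported as confirming cardiometabolic benefit.
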